### Ethical issues

The overarching ELANS protocol was approved by the Western Institutional Review Board (#20140605) and is registered at Clinical Trials (#NCT02226627). Each site-specific protocol was also approved by the ethical review boards of the participating institutions. All participants provided informed consent/assent for participation in their country-level study. Participant confidentiality for the pooled data is maintained via the use of numeric identification codes rather than names. All data transfer was done with a secure file sharing system.

### Data collection instruments

The ELANS protocol includes data collected via questionnaires and objective measurements. The questionnaires were administered in 2 household visits (Fig. 2). The first visit involved the selection of a respondent within the household. Additionally, the first visit also included application of the SEL questionnaire and 24-h dietary recall (24-h), and assessment of anthropometric measurements. In the first visit, a subsample received instructions regarding the use of an accelerometer with a diary to be filled out for 7 consecutive days. The second visit was performed 8 days after the first contact for the participants who were given accelerometers and 4 days later for the participants who were not given accelerometers. The second visit also included the administration of a second 24-h, the IPAQ-Long Questionnaire, and a beverage intake questionnaire (BEVQ) and the retrieval of the accelerometer.

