### Dietary assessment

The 24-h method was selected because of its nearly universal applicability across populations with varying literacy skills and its relatively low burden for participants [28]. Each recall was conducted using the Multiple Pass Method [29] and ascertained all foods, nonalcoholic and alcoholic beverages, water and dietary supplements consumed over the prior 24 h in depth. The BEVQ was designed to obtain the frequency of beverage intake across 10 beverage categories (water, flavored water, soft drinks, fruit drinks, sport drinks, energy drinks, tea and coffee drinks, other non-alcoholic drinks, and alcoholic drinks). For each beverage, participants answered whether they consume the specific category of beverage, the frequency of intake (daily, weekly, monthly), and how often they drink the beverage during the selected unit (1–10 occasions). The list of beverages included in the questionnaire was standardized as much as possible across the ELANS countries; however, regional variations in beverage consumption patterns required some cultural and regional adaptations for some items within beverage categories.

The food and beverages intakes recorded with the 24-h is transformed into energy, macronutrients and micronutrients values using the Nutrition Data System for Research version 2013 software (NDS-R, University of Minnesota, MN). A food matching standardized procedure involving nutritional equivalency of local food items reported by the study participants into foods available in NDS-R database was strictly conducted by each country, and describe in detail elsewhere [30]. A concordance rate of at least 80 % to 120 % for energy and macronutrient content was required to establish a nutritional equivalency of local food items to foods available in NDS-R database.

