The Multiple Source Method (MSM) was used to estimate the usual intake of each nutrient, food and food groups. The method was developed by researchers at the European Prospective Investigation into Cancer and Nutrition (EPIC) The MSM method is a mixed model comprised of three parts which requires at least two days of short-term dietary measurements (such as 24-h) on a random subsample of the target population. In the first part, the probability of consumption of a food/nutrient on a day is estimated using logistic regression with random effects (probability model). Second, data that has been transformed for normality is used to estimate usual amount of food intake on days of consumption using linear regression, also with random effects (quantity model). In the final part, the individual usual food/nutrient intake is calculated by multiplying the probability of consumption of a food/nutrient (part 1) with the usual amount of food intake (part 2) [31]. The means and percentiles of the intakes will be estimated for each sex. The MSM method is a web-based statistical modeling, available at MSM website (https://msm.dife.de/tps/en).

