#### Objectively assessed activity

To objectively monitor physical activity and inactivity, 40 % of the sample was asked to wear a triaxial accelerometer (model GT3X+, ActiGraph, Pensacola, FL, USA) on an elasticized belt at hip level on the right mid-axillary line for 7 days. The participants were asked to wear the device while they are awake and to take it off for sleeping, showering or swimming. Verbal (in person and by demonstration) and written instructions on how to wear the accelerometer were provided. To further ensure protocol compliance, participants filled in an accelerometer log indicating the start- and end-time of use per day. Following the final day of data collection, the accelerometers was returned to the study sites, and the research team verified the data for completeness using the ActiLife software version 6 (ActiGraph, Pensacola, FL). At least 5 days of recording with a minimum of 10 or more hours of registration per day including at least one weekend day were required for data inclusion and analysis. The sampling interval (epoch) was set at 30 records per second.

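### The 8-day and 4-day gaps between recalls tie the weekday/weekend pairing of recalled days to accelerometer status; the effect on usual-intake estimates is minor and a day-type term would remove it.

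*Protocol article*

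**What the plan says.** All places are in the protocol article.

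- **Data collection instruments.** One 24-hour recall is given at each of two household visits. On timing: "The second visit was performed 8 days after the first contact for the participants who were given accelerometers and 4 days later for the participants". The second group in that sentence is the people without a device. On content: "The second visit also included the administration of a second 24-h".
- **Dietary assessment.** Each recall covers what was "consumed over the prior 24 h in depth". The recalls then feed one model: "The Multiple Source Method (MSM) was used to estimate the usual intake of each nutrient, food and food groups". That model has a logistic part for the probability of consumption and a linear part for the amount, both with random effects.
- **Objectively assessed activity.** The device was given to 40% of the sample for 7 days. For a record to be usable, "At least 5 days of recording with a minimum of 10 or more hours of registration per day including at least one weekend day were" needed.

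The article gives no figure for weekend coverage of the recalls and does not say on which days of the week visits were made.

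**The concern.** Eight days is one week plus one day. A wearer's second recalled day is therefore always the next day of the week after the first. For a non-wearer it is always four days of the week later. Which days are paired within a person thus depends on a logistic fact, namely whether that person carried a device.

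The MSM uses the pairs to separate day-to-day variation from stable differences between people. If intake differs between weekdays and weekends, pairs of the same day type make that difference look like a stable trait, and mixed pairs make it look like daily noise. Wearers have too few mixed pairs and non-wearers too many.

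This touches the usual-intake percentiles, analyses confined to wearers, and wearer versus non-wearer comparisons. It bears on the third study aim (intake, expenditure and anthropometry) whenever objective activity data are used. If first visits were not spread evenly over the week, mean intake could also differ by device status.

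**Working it through.** **Inputs from the article.** Gaps of 8 and 4 days; one recall per visit, covering the prior 24 hours (taken as the day before the visit); 40% wearers, hence 60% non-wearers. The article has no figure of its own to reproduce here.

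**Assumptions.** Weekend means Saturday and Sunday. The distribution of first-visit days is not given, so several are tried. Let d be the weekend-minus-weekday difference in intake; its size is not given either.

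**Step 1: pairs, first visits even over 7 days.** Recalled days, by first-visit day from Monday to Sunday:
- 8-day gap: Sun/Mon, Mon/Tue, Tue/Wed, Wed/Thu, Thu/Fri, Fri/Sat, Sat/Sun.
- 4-day gap: Sun/Thu, Mon/Fri, Tue/Sat, Wed/Sun, Thu/Mon, Fri/Tue, Sat/Wed.

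| | No weekend day | Mixed | Both weekend | Weekend share of recalls |
|---|---|---|---|---|
| Wearers (8 d) | 4/7 = 57% | 2/7 = 29% | 1/7 = 14% | 4/14 = 2/7 |
| Non-wearers (4 d) | 3/7 = 43% | 4/7 = 57% | 0 | 4/14 = 2/7 |
| Two independent days | (5/7)² = 51% | 2(2/7)(5/7) = 41% | (2/7)² = 8% | 2/7 |

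Pooled share with no weekend recall: 0.4 × 4/7 + 0.6 × 3/7 = 48.6%.

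**Step 2: effect on variance components.**
- Within-person part due to day type = (share of mixed pairs) × d²/2. Wearers 0.143d², non-wearers 0.286d², independent days 0.204d².
- Spurious covariance between the two recalls = P(both weekend) − (2/7)². Wearers 1/7 − 4/49 = +0.061d². Non-wearers 0 − 4/49 = −0.082d².
- Pooled: 0.4 × 0.061 + 0.6 × (−0.082) = about −0.024d², so the errors partly cancel if everyone is modelled together.

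**Step 3: size in kcal.** Assume d = 200 kcal, a true between-person SD of 300 or 500 kcal, and a normal distribution, so the 95th percentile lies 1.645 SD above the mean. The spurious covariances are 0.0612 × 40,000 = +2,449 and −0.0816 × 40,000 = −3,265 kcal².
- SD 300, wearers: 1.645 × (√92,449 − 300) = +6.7 kcal. Non-wearers: 1.645 × (√86,735 − 300) = −9.0 kcal.
- SD 500, wearers: 1.645 × (√252,449 − 500) = +4.0 kcal. Non-wearers: 1.645 × (√246,735 − 500) = −5.4 kcal.

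These apply if the variance is estimated within each group; a pooled fit gives less, because of the cancellation in Step 2.

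**Step 4: uneven first visits (all assumptions).**

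| First visits | Weekend share, wearers | Weekend share, non-wearers | No weekend recall, overall |
|---|---|---|---|
| Even over 7 days | 28.6% | 28.6% | 48.6% |
| Mon–Fri, second visit any day | 10% | 30% | 56% |
| Mon–Sat, second visit any day | 17% | 25% | 57% |
| Both visits Mon–Sat | 10% | 20% | 68% |
| Half of first visits on Sat/Sun | 42.5% | 27.5% | 43% |

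In the Monday-to-Friday case the means of the two groups differ by (0.30 − 0.10) × d = 0.20d, or 40 kcal at d = 200. Against a true weekend share of 2/7, wearers are about (0.286 − 0.10) × 200 = 37 kcal too low. In the last row the direction reverses.

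**The case against.** The case for leaving this alone is strong on size.

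- With even visits the gap biases no group mean. Under the assumptions above plus a within-person SD of 600 kcal, the two groups' within-person variances differ by 0.5 × (4/7 − 2/7) × 200² = 5,714 kcal², which is 1.6% of 360,000. Estimates are described by sex, not by device status, so the distortions partly offset. This stands, and it is why the point is minor.
- A reader might infer that about half the sample lacking a weekend recall is a fault of the gaps. It is not: 48.6% is close to the 51% expected for any two independent days. It reflects having only two recalls.
- A reader might infer that wearers are always the more weekday-only group. That depends on the schedule. With half of first visits on Saturday or Sunday, 40% of wearers and 45% of non-wearers have no weekend recall.
- A reader might see a contradiction with the weekend rule for accelerometer data. That rule is a validity criterion for a 7-day record, and a one-day recall cannot meet an equivalent one. Nor does the third aim rest on wearers alone, since the physical activity questionnaire is listed at the second visit without restriction to them.
- The article is condensed and refers to a manual of operations. Allocation of visit days and MSM covariates may be settled there, so silence on them is not held against the plan.

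The pairing itself survives all of this, because it follows from the two stated gaps and needs no assumption about visit days.

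**Conclusion.** The point holds in a limited form. The stated gaps tie the pairing of recalled days to device status, with mixed pairs in 29% of wearers and 57% of non-wearers under even visits. This pushes the MSM variance components in opposite directions. The consequence is small: about 4 to 9 kcal at the 95th percentile under the assumed values, and less in a pooled fit.

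The potentially larger effect is a difference in mean intake by device status, and it arises only if first visits were uneven over the week. The documents do not say that they were, so the 10% versus 30% weekend shares are an illustration, not a finding. Severity: minor.

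**What to change.** Fieldwork is described as ending, so the remedy is analytic.

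1. Classify each recalled day as weekday or weekend from the visit date (assumed to be recorded; the article does not say so) and enter this as a covariate in both the probability and the amount part of the MSM.
2. Standardise each person's usual intake to a week of five weekdays and two weekend days.
3. Apply the same 5:2 weighting to accelerometer averages whenever intake is related to objective activity.

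This removes the pairing artefact to the extent that it comes from a weekday/weekend difference. It also guards against a shift in means if visits were uneven. The cost is one extra parameter in each MSM part and slightly more analysis work. The article describes the MSM as a web-based tool, so whether it accepts a covariate that varies between a person's recalls should be checked first. If the full plan already contains such a term, one sentence saying so settles the point.

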**Fig. 2 Fig2:**
[figure not shown]
Study design

### Dietary assessment

The 24-h method was selected because of its nearly universal applicability across populations with varying literacy skills and its relatively low burden for participants [28]. Each recall was conducted using the Multiple Pass Method [29] and ascertained all foods, nonalcoholic and alcoholic beverages, water and dietary supplements consumed over the prior 24 h in depth. The BEVQ was designed to obtain the frequency of beverage intake across 10 beverage categories (water, flavored water, soft drinks, fruit drinks, sport drinks, energy drinks, tea and coffee drinks, other non-alcoholic drinks, and alcoholic drinks). For each beverage, participants answered whether they consume the specific category of beverage, the frequency of intake (daily, weekly, monthly), and how often they drink the beverage during the selected unit (1–10 occasions). The list of beverages included in the questionnaire was standardized as much as possible across the ELANS countries; however, regional variations in beverage consumption patterns required some cultural and regional adaptations for some items within beverage categories.

The food and beverages intakes recorded with the 24-h is transformed into energy, macronutrients and micronutrients values using the Nutrition Data System for Research version 2013 software (NDS-R, University of Minnesota, MN). A food matching standardized procedure involving nutritional equivalency of local food items reported by the study participants into foods available in NDS-R database was strictly conducted by each country, and describe in detail elsewhere [30]. A concordance rate of at least 80 % to 120 % for energy and macronutrient content was required to establish a nutritional equivalency of local food items to foods available in NDS-R database.

The Multiple Source Method (MSM) was used to estimate the usual intake of each nutrient, food and food groups. The method was developed by researchers at the European Prospective Investigation into Cancer and Nutrition (EPIC) The MSM method is a mixed model comprised of three parts which requires at least two days of short-term dietary measurements (such as 24-h) on a random subsample of the target population. In the first part, the probability of consumption of a food/nutrient on a day is estimated using logistic regression with random effects (probability model). Second, data that has been transformed for normality is used to estimate usual amount of food intake on days of consumption using linear regression, also with random effects (quantity model). In the final part, the individual usual food/nutrient intake is calculated by multiplying the probability of consumption of a food/nutrient (part 1) with the usual amount of food intake (part 2) [31]. The means and percentiles of the intakes will be estimated for each sex. The MSM method is a web-based statistical modeling, available at MSM website (https://msm.dife.de/tps/en).

### Physical activity measures

#### Self-reported activities

Self-reported physical activity was assessed using the International Physical Activity Questionnaire (IPAQ)-long version, a validated self-report measurement tool for physical activity in Latin America [32]. The Mexican (Spanish) version of IPAQ [33] was adapted for all countries of ELANS, using culturally appropriate wording and examples. Only the sections leisure-time and transport physical activity (LTPA and TPA) were included, due to greater importance of these domains in public health and poor validity of the occupational and home-based PA IPAQ sections in Latin American urban settings. These sections are the most relevant for categorizing population levels of physical activity and for guiding public health policies and programs [32].

A domain-specific activity score is calculated separately for each domain of physical activity (transportation and leisure-time). Total times engaged in walking, moderate physical activity and vigorous physical activity, all expressed in min/week, are scored using established methods posted at the IPAQ website (www.ipaq.ki.se).

Additionally, information not included as part of the summary score of physical activity, such as sedentary activities (reading, television viewing and sitting at a desk), will be analyzed.

#### Objectively assessed activity

To objectively monitor physical activity and inactivity, 40 % of the sample was asked to wear a triaxial accelerometer (model GT3X+, ActiGraph, Pensacola, FL, USA) on an elasticized belt at hip level on the right mid-axillary line for 7 days. The participants were asked to wear the device while they are awake and to take it off for sleeping, showering or swimming. Verbal (in person and by demonstration) and written instructions on how to wear the accelerometer were provided. To further ensure protocol compliance, participants filled in an accelerometer log indicating the start- and end-time of use per day. Following the final day of data collection, the accelerometers was returned to the study sites, and the research team verified the data for completeness using the ActiLife software version 6 (ActiGraph, Pensacola, FL). At least 5 days of recording with a minimum of 10 or more hours of registration per day including at least one weekend day were required for data inclusion and analysis. The sampling interval (epoch) was set at 30 records per second.

### Anthropometric measurements

In each country, the anthropometric measurements of body weight, height and waist, hip and neck circumferences were collected according to standardized procedures. The participants were measured after all heavy clothing, pocket items and shoes and socks are removed. Body weight was measured with a calibrated electronic scale up to 200 kg with an accuracy of 0.1 kg. Height was measured with a portable stadiometer up to 205 cm with an accuracy of 0.1 cm. The measurements were taken during inspiration, with the base of the stadiometer lightly touching the upper reaches of the head and with the participant’s head in the Frankfort Plane [34]. The circumferences were measured with an inelastic tape to the nearest 0.1 cm. Waist circumference was measured according to World Health Organization recommendations, i.e., with the participants standing, after a regular expiration, to the nearest cm, midway between the lowest rib and the iliac crest [35]. Hip circumference was recorded at the level of the greatest posterior protuberance of the buttocks, with the tape held horizontally flat without pressing the soft tissues. Neck circumference was measured at the point just below the larynx (thyroid cartilage) and perpendicular to the long axis of the neck (with the tape line in the front of the neck at the same height as the tape line at the back of the neck) [36].

The interviewers were trained to collect all measurements by certified nutritionists/dietitians who will simultaneously operate as supervisors of the fieldwork. Each measurement was repeated twice to ensure accuracy, and the average used for the analyses. If the two readings differ by more than the previously established set point (0.1 kg for weight, 0.5 cm for height, 0.5 cm for neck circumferences, and 1 cm for waist and hip circumferences), then a third measurement was taken. All three measurements were recorded, and the outlier excluded during the data cleaning process.

The body mass index (BMI; weight (kg)/height (m^2^)) and waist-to-hip ratio were calculated. The absolute values of each circumference measurement were compared to predefined cutoff points according to age and gender.

### Demographics and SEL

A questionnaire was used to collect information about demographics such as age, gender, years of education, number of people in the household, race/ethnicity, marital status, and number of years living in the country.

Socioeconomic level was also evaluated by questionnaire using a format that will be country-dependent and based on the legislative requirements or established local standard layouts. SEL data was divided into three strata (high, medium and low) based on the national indexes used in each country [37–43].

### Pilot study

To examine all procedures and verify that the planned activities could be adequately executed, a pilot study was performed on 50 participants from each country 2 months before starting data gathering for the full study protocol. This pre-test included all procedures from the selection of volunteers to the analyses of data consistency. Principal investigators of each country provided information, their opinion and experience with regard to data collection. This pilot study allowed for the fine-tuning of the study protocol, among other things, the pilot test allowed measurement of the time required for the execution of various activities, for example the first and second visit, data transfer from the pollster to the investigator, the review and survey data entry. It also allowed verification of the exactitude of the data collected and identification of the issues that should be emphasized for the second training session for pollsters, prior to the beginning of the study. The results of this process did not reveal the need to implement any changes in the proposed methodology. Due to the lack of security in many cities, it was verified the need for greater identification of interviewers (badges, cover letter, apron lab coat).

### Study management

The management of ELANS was designed to ensure effective collaboration and communication between the eight study centers involved in this cross-sectional study. Investigators from each participating center were involved in the planning and development of the protocol, which included the study design.

Two chairs (from Argentina and Brazil) and a co-chair (from Costa Rica) are responsible for the overall coordination of the study. Each study site is managed by a local principal investigator (PI), who is responsible for all aspects of data collection at the local level.

A database center is responsible for the creation and management of a central database in Argentina. Two researchers in Brazil are responsible for the management of a central database and for the analysis of the accelerometer data. A statistician and his team in Brazil are responsible for the data analysis and the generation of preliminary reports.

To facilitate data collection, entry and management, a secured web-based system was used. Data from each study site entered remotely using a standard File Transfer Protocol (FTP) web-browser, and the system allowed both the study site staff and the coordinating center to monitor the progress and generate missing data reports in real time.

A steering committee of four external advisors with extensive and diverse scientific background was invited to assess the overall progress of the study and to provide guidance regarding the overall study direction and study goals. External advisor had expertise in designing multicentric epidemiological studies, nutrition and physical activity survey, and statistical analysis.

With the exception of requiring that the study be global in nature, the study sponsor had or will have no role in the study design, data collection and analysis, decision to publish, presentation and/or manuscript preparation.

Once the study is complete, the data will be available for sharing with the international scientific community.

